## Assignment of interventions: allocation

### Sequence generation {16a}

The randomisation system was created in collaboration with the trial analysts and the CIs and will be maintained by the KCTU for the duration of the project, hosted on a dedicated server within King’s College London (KCL). Randomisation is at the level of the individual, independent, and concealed using the method of random permuted blocks which are unknown to the study team. It is stratified by site and diagnosis.

### Concealment mechanism {16b}

After obtaining written informed consent, completing the baseline assessment measures, and confirming eligibility within the trial team, RAs contact participants to inform them of the outcome. RAs then randomise participants within 2 working days using a trial-specific web-based portal developed and hosted by the KCTU.

### Implementation {16c}

Following randomisation, allocations are made known by email to the trial therapists, the trial manager (to monitor adherence to the randomisation algorithm), the trial administrators (who are delegated to post allocation letters), and the PIs and CIs (to ensure oversight). The allocation is also made known to participants by phone call and follow-up letter from an unblinded staff member, and to relevant individuals from their healthcare team.

## Assignment of interventions: blinding

### Who will be blinded {17a}

Talking With Voices is a single-blind (assessor) RCT. Blinding of the allocation code will be maintained for RAs until all outcome measures for all participants have been collected, and is managed using a range of measures, such as separate offices for therapists and RAs, protocols for answering telephones (including reminders for participants, family members, and clinicians about the blind), protocols for message taking and secretarial support, separate diaries and pigeonholes, and data file security using passwords and encryption of randomisation information. Further, all qualitative interviews with trial participants will occur at a timepoint away from a standard follow-up point and will be overseen by the trial manager to ensure participants and the RAs are not in contact.

The senior trial statistician will be unaware of individual participants’ random allocations or group-level summary data split by arm throughout the course of the trial. The trial statistician will be blinded during the drafting of the Statistical Analysis Plan (SAP) and become unblinded to the individual participant and group-level summary data at the preparation of the first closed DMEC report (approximately 1 year after first participant recruitment). The primary database will also not include any information about allocation, which is contained in a separate system to protect against accidental unblinding, with a secondary database maintained for entering unblinded information (e.g. adverse events, therapy details) which blinded researchers do not have access to. Final analyses will be carried out by the trial statistician and overseen by the senior trial statistician, with investigators and the research team blind to group-level summary data split by arm throughout the course of the trial. A SOP for maintaining, recording, and managing blinding has been developed to outline these procedures, which will be made available to the oversight committees on request and has been received by trial staff as confirmation they understand and will comply with the protocols.

Staff are required to report all blind breaks, which are recorded by the trial manager and reviewed by the CIs for any patterns in unblinding. The DMEC and TSC also monitor unblindings and implement corrective action if necessary. There are only two follow-ups scheduled (at 8 months and 14 months, both after end of treatment), which further reduce the risk of blind breaks by removing the opportunity for therapists and RAs to cross paths while visiting participants at their homes and/or when communicating with participants to arrange visits. All letters to participants and clinicians contain a standardised statement about the need to maintain the single blinding process. In the event of blind breaks, we aim to identify independent assessors to complete subsequent follow-ups (subject to any threats to participant engagement with follow-up). If a change of assessor is not possible, the assessment is audio-recorded with the participant’s permission and another assessor co-rates the PSYRATS-AH and Psychotic Symptoms Rating Scale—Multimodal Hallucinations ([PSYRATS-MMH]: the only assessment measures which are interviewer-rated, rather than participant-rated). Scores are then compared across the blinded and unblinded RAs, with any discrepancies taken to the trial manager for discussion and resolution.

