#### Training and supervision of assessors

RAs require a bachelor level degree in psychology, or another related discipline, and experience of working in health and social care settings. All RAs received trial-specific research and clinical training from the trial manager and a lived experience expert at trial commencement and 15 months into the trial, including training on trial SOPs and all outcome measures, in order to promote GCP compliance and data quality. RAs also receive regular supervision from site PIs and weekly 60-min individual supervision from the trial manager (focussing on such areas as safeguarding, risk management, and ensuring any participant distress which may arise throughout assessments is appropriately addressed; compliance to the trial protocol, SOPs, and local NHS policy; outcome measure queries and scoring questions; eligibility queries and reviews; monitoring assessment, liaison and retention and problem-solving any issues; and maintaining personal wellbeing). In addition, they also attend monthly group supervision facilitated by the trial manager to promote reflective practice, peer connection and shared learning across sites, and attend monthly group inter-rater reliability training for the PSYRATS-AH. To aid with the latter process, assessments may be audio-recorded with participant permission to check the quality and reliability of the assessment and scores.

Both trial therapists and RAs are NHS employed members of staff and are required to keep updated with Trust-approved mandatory training. All members of trial staff complete training in GCP and are required to familiarise themselves with the trial protocol, SOPs, and relevant trial-specific manuals for their role.

Trainee clinical psychologists will conduct the qualitative interviews with participants while drawing on appropriate supervision and support from members of the trial team. The therapist focus group will be convened by an NHS worker with lived experience of voice-hearing and/or psychosis and experience of qualitative research. The qualitative researchers will meet regularly with their supervisors to support their data collection and development of the interview schedule throughout the course of the studies, as well as supporting the development of emerging thematic and conceptual outputs.

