All (S)AEs are reported and monitored at monthly TMG meetings and at each meeting of the DMEC. The chair of the DMEC will also be informed of any SAEs that are deemed possibly or probably related to trial procedures or intervention in between meetings. It has been agreed between the TSC and DMEC committees that in the event of a pattern or significant number of related SAEs, a different procedure of independent monitoring may be agreed upon. SAEs are reported by the trial manager or CIs to the study sponsor as soon as possible (typically within 24 h) and SAEs classified as both unanticipated and related to study procedures will be reported to the REC/ HRA within 15 calendar days. Such events will also be reported to the REC/HRA immediately (and no later than two calendar days) for incidents that indicate risk of imminent death, serious injury, or serious illness, and require prompt remedial action for other participants. The AE database was made available to the sponsor for audit purposes in spring 2024 and a report of all AEs will be made available to the sponsor on request. All AEs and SAEs are entered by the trial manager onto the unblinded therapy attendance MACRO database and are reported during DMEC meetings. These processes aim to provide independent scrutiny of (S)AEs at different levels throughout the duration of the trial. Within the trial’s outcome publication, we will report details of all events classified as AEs and SAEs, regardless of expectedness or relatedness to study procedures or intervention.

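### Where a PSYRATS assessment is co-rated after a blind break, disagreements between the blinded and unblinded ratings go to a trial manager who knows the allocations

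*Protocol article*

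**What the plan says.** The section on who will be blinded ({17a}) describes a single-blind trial in which the research assistants (RAs) who assess outcomes stay blind until data collection is complete. It sets two remedies for a blind break, in order.

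- **First remedy.** "In the event of blind breaks, we aim to identify independent assessors to complete subsequent follow-ups". No adjudication is involved.
- **Fallback.** "If a change of assessor is not possible, the assessment is audio-recorded with" the participant's permission, and another assessor co-rates PSYRATS-AH and PSYRATS-MMH. The article calls these "the only assessment measures which are interviewer-rated, rather than participant-rated".

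Where the two sets of ratings differ, the rule is: "Scores are then compared across the blinded and unblinded RAs, with any discrepancies taken to the trial manager for discussion and resolution".

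Two other sections establish what the trial manager knows. Under Implementation {16c}, after randomisation "allocations are made known by email to the trial therapists, the trial manager (to monitor adherence to the randomisation algorithm"), among others. Under Adverse event reporting and harms {22}, "All AEs and SAEs are entered by the trial manager onto the unblinded therapy attendance MACRO database". Section {17a} says that blinded researchers have no access to the database that holds unblinded information.

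**The concern.** Co-rating from a recording serves to recover a score from someone who does not know the arm, after the original assessor has learned it. Once the co-rating is done, that score exists. The article does not say that it stands. It is compared with the unblinded score, and any difference goes to a person who knows the allocation.

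When the two ratings agree, the choice between them makes no difference. When they disagree, the safeguard has work to do, and that is where knowledge of the arm can come back in.

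What is at stake is the two scales that assessor blinding most directly protects. Participants know their arm and the other measures are participant-rated. PSYRATS-AH is the first secondary outcome listed and bears on the first secondary efficacy hypothesis, improvement in distressing voices.

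**Working it through.** The article gives no figure to reproduce, so the check sets its statements side by side.

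1. **Does the trial manager know the arm?** Yes, on two separate statements: the allocation email ({16c}) and data entry in the unblinded database ({22}). Section {17a} adds that the trial manager records all blind breaks, and so would know which assessments are involved.
2. **Does the trial manager take part in settling the score?** Yes: "with any discrepancies taken to the trial manager for discussion and resolution" ({17a}). The wording allows either a decision by the trial manager or a consensus that the trial manager leads. In both cases someone who knows the arm takes part, and in a consensus the unblinded RA may do so too.
3. **Is there a stated safeguard at this step?** The article does not say that the blinded score prevails, that the trial manager is masked to the participant's arm, or that a rater without access to allocation decides.
4. **Which outcomes are touched?** PSYRATS-AH and PSYRATS-MMH, both listed as secondary outcomes in {18a}. The primary outcome is the QPR total at 8 months, which is self-reported and does not pass through this step.
5. **Which assessments are touched?** Only those that meet every condition: the blind was broken, the assessor could not be changed, the participant allowed recording, and the two ratings differed. As a formula:

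   share adjudicated = P(blind break) × P(not reassigned, given a break) × P(recorded, given not reassigned) × P(ratings differ, given recorded)

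   shift in an arm's mean from this route = share adjudicated in that arm × mean change in score that resolution makes relative to the blinded score

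   The between-arm bias is the difference of this product between arms. The documents give none of these terms. Each of the last three probabilities is at most 1, so the share adjudicated cannot exceed the blind-break rate and may be well below it. The direction is also not given, because some discrepancies may be resolved to the blinded score.

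The section on training and supervision of assessors also lists "outcome measure queries and scoring questions" among the topics of the RAs' weekly supervision by the trial manager. This is context only. It is one item in a general list and does not show that the trial manager sets individual participants' scores.

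**The case against.** The strongest case on the other side has four parts.

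- **The route is a narrow fallback.** Reassignment to an independent assessor comes first, and the oversight committees monitor unblinding and can require corrective action. This stands. It limits how many ratings are affected but does not make the rule sound for those that reach it.
- **Resolution may be a consensus.** This also stands. A reader might infer that the trial manager alone fixes the final value or overrides the blinded rater, and the article does not say so. The point needs only that a person who knows the arm can influence the score.
- **The blinding SOP may cover it.** Section {17a} refers to an SOP on blinding that is not shown, and it may mask this step. But the article does more than leave a detail to the SOP: it states a rule and names an unblinded role in it. If the SOP says otherwise, the two texts need to be reconciled.
- **The outcomes are secondary and the effect is unquantified.** Both are true. They bear on how much weight to give the point, not on whether it holds.

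A reader might go further and infer that the trial is left with no outcome free of allocation knowledge. The documents do not support that. PSYRATS ratings made by an RA whose blind held never enter this route, and neither do those made by a replacement assessor who is still blind. A flaw in a fallback for a subset of ratings is not a loss of blinding for the whole outcome.

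**Conclusion.** The point holds in a limited form. For PSYRATS-AH and PSYRATS-MMH assessments that follow a blind break, cannot be reassigned, are recorded and yield discrepant ratings, the stated rule lets knowledge of allocation influence the final score although a blinded score is available. The primary analysis of the QPR is untouched.

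The size and direction of any bias cannot be estimated from the documents. A numerical range would need an assumed adjudicated share and an assumed shift, neither with a source in the article, and putting the blind-break rate in place of the adjudicated share would overstate it.

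The conclusion rests on the article as written and assumes that no masking at this step is specified elsewhere. The change is worth making because it is cheap and removes a foreseeable criticism of the observer-rated outcomes.

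**What to change.** **Rule.** State in the blinding SOP and in the SAP, which the article describes as in preparation, that where an assessment is co-rated after a blind break, the blinded co-rater's score is the one analysed. Keep both scores and use the unblinded one only to report agreement. If a discrepancy must be discussed, send it to an existing rater who has no access to allocation.

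**Assessments already resolved.** Recruitment closed on 30 June 2025 and the last visit is due in January 2026, so some ratings may already have been settled under the present rule. For these, use the original blinded score where it was kept. Flag all affected ratings, report how many there are by arm, and repeat the PSYRATS analyses without them as a sensitivity check.

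**Cost.** No new rater is needed, since the co-rating is already planned. The future rule is a change of wording. The retrospective part means finding the original blinded ratings, and the article does not say whether they are retained.

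**What it does not cure.** The co-rater scores an interview conducted by an unblinded RA. That RA's questioning can shape what is recorded, and the participant may reveal the arm on the recording. Using the blinded score removes the adjudication route but not these influences.

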### Procedure for unblinding if needed {17b}

The blind will only be deliberately broken in very exceptional circumstances in which clinical duty of care or participant rights overrule the rationale for the blind. Any deliberate blind breaks, and the procedure for breaking the blind, will be the decision of the trial manager and CIs on a case-by-case basis.

## Data collection and management

### Plans for assessment and collection of outcomes {18a}

After recruitment and baseline assessments are concluded, a follow-up assessment will take place at 8 months post-randomisation (end of treatment). Additional follow-up assessments will be performed at 14 months post-randomisation, dependent upon when participants were recruited into the trial (thus, the total follow-up period will vary from 14 to 8 months, maximising the recruitment period and providing best value for money). In view of this, we anticipate 14-month follow-up data on approximately the first 207 participants.

#### Primary outcome

The primary outcome will be the total score on the 15-item QPR at 8 months, using an analysis metric of mean change from baseline.[49] The QPR was developed in collaboration with service users to assess personal recovery from psychosis, containing items that were initially derived from qualitative interviews about this topic. It has excellent reliability, validity, and sensitivity to change and is nationally adopted as a Patient Recorded Outcome Measure for evaluation of early intervention for psychosis services, forming part of the Mental Health Services Data Set. Patients consistently prioritise personal recovery over specific symptom change [67] and the QPR has been cited [68] as the only measure of recovery that directly maps onto all 5 processes of the influential CHIME framework of personal recovery [69].

#### Secondary outcomes

Secondary outcomes will assess overall voice severity and other relevant dimensions of psychiatric distress and trauma sequalae, assessed as mean Changes from baseline at 8 months (primary endpoint) and 14 months (secondary endpoint). With the exception of the unpublished PSYRATS-MMH, all are standardised semi-structured interviews and questionnaires with demonstrated reliability and validity.The PSYRATS-AH [54], an interviewer-rated measure that assesses voices across 11 domains of phenomenology and impact.The Voices Acceptance and Action Scale - Brief Version (VAAS-12) [64], a 12-item measure designed to assess acceptance-based attitudes and actions in relation to auditory and command hallucinations.The PSYRATS-MMH, an unpublished scale adapted from PSYRATS-AH for assessing the presence and impact of non-auditory hallucinations.The PTSD Checklist for DSM-5 (PCL-5) [61], a 20-item self-report measure that assesses the severity of a range of trauma-related symptoms.The Trauma Voice Associations Questionnaire (TVAQ) [57], a 16-item inventory which assesses connections between adverse life events and voice hearing experiences.The Dissociative Experiences Scale-II (DES-II) [63], a 28-item measure assessing the daily frequency of dissociation across the domains of absorption, depersonalisation/derealisation, and dissociative amnesia.

The proposed mechanisms of action for TWV will also be measured with the following instruments:Negative beliefs about the self will be assessed with The Brief Core Schema Scale (BCSS) [62], a 12-item self-report questionnaire.Dissociative experiences will be measured with the depersonalisation/derealisation subscale of the DES-II [63], which contains 6 items scored for daily frequency.Interactions with one’s voices will be assessed with the Beliefs About Voices Questionnaire – Revised (BAVQ-R) [59], a 35-item measure of beliefs about auditory hallucinations and emotional and behavioural reactions to them.Assertiveness in response to one’s voices will be assessed using the 15-item Approve – Voices Questionnaire [58].

Additional pharmacological and psychological treatments for mental health concerns will be monitored in both arms using a treatment documentation sheet, with feedback about the trial and intervention, including potential adverse effects of participation, collected via a self-report “Learning From You” questionnaire offered to participants on exit from the study following the 8- or 14-month assessment. Copies of both these measures are available from the corresponding author on request. Adverse events (AEs) and SAEs will also be assessed separately (for details, please see “Adverse event reporting and harms {22}”).

#### Baseline characteristics

In addition to a measure of demographic characteristics, the Modified Trauma and Life Events Checklist (TALE) [60], a 21-item trauma screening tool for identifying clinically significant traumas in people with psychosis, will be administered at baseline.

#### Experiences of receiving and delivering therapy

The qualitative studies will be guided by semi-structured, flexible topic guides which may be revised iteratively throughout the process of data collection and analysis to respond flexibly to novel topics and themes of interest. Individual interviews will be used to explore participants’ experience of the trial and intervention, including any perceived positive and negative aspects; therapy components they have implemented into their lives; recommendations for improvement; any perceived impact on their personal recovery and mental health (with an emphasis on the hypothesised mechanisms of dissociation, negative self-beliefs, and dysfunctional patterns of voice relating) during and following TWV therapy; if and how the intervention may have contributed to these changes, and to draw patterns across participants’ experiences. A second series of qualitative interviews will explore the influence of minoritised ethnic heritage on receiving and engaging with TWV therapy, and a third focus group study will examine key themes associated with the delivery and implementation of TWV within NHS services from the perspective of trial therapists. All qualitative data will be audio-recorded with participants’ consent and transcribed verbatim for analysis.

#### Training and supervision of assessors

RAs require a bachelor level degree in psychology, or another related discipline, and experience of working in health and social care settings. All RAs received trial-specific research and clinical training from the trial manager and a lived experience expert at trial commencement and 15 months into the trial, including training on trial SOPs and all outcome measures, in order to promote GCP compliance and data quality. RAs also receive regular supervision from site PIs and weekly 60-min individual supervision from the trial manager (focussing on such areas as safeguarding, risk management, and ensuring any participant distress which may arise throughout assessments is appropriately addressed; compliance to the trial protocol, SOPs, and local NHS policy; outcome measure queries and scoring questions; eligibility queries and reviews; monitoring assessment, liaison and retention and problem-solving any issues; and maintaining personal wellbeing). In addition, they also attend monthly group supervision facilitated by the trial manager to promote reflective practice, peer connection and shared learning across sites, and attend monthly group inter-rater reliability training for the PSYRATS-AH. To aid with the latter process, assessments may be audio-recorded with participant permission to check the quality and reliability of the assessment and scores.

Both trial therapists and RAs are NHS employed members of staff and are required to keep updated with Trust-approved mandatory training. All members of trial staff complete training in GCP and are required to familiarise themselves with the trial protocol, SOPs, and relevant trial-specific manuals for their role.

Trainee clinical psychologists will conduct the qualitative interviews with participants while drawing on appropriate supervision and support from members of the trial team. The therapist focus group will be convened by an NHS worker with lived experience of voice-hearing and/or psychosis and experience of qualitative research. The qualitative researchers will meet regularly with their supervisors to support their data collection and development of the interview schedule throughout the course of the studies, as well as supporting the development of emerging thematic and conceptual outputs.

